### Intervention groups

#### Intervention group 1 (IG1)

This group receives oral health promotional material at the time of recruitment. This group also receives a **midwifery intervention** (MIOH) which involves midwives providing the following at the 1^st^ antenatal visit:

*Oral health education*: Midwives re-emphasise the importance of maternal oral health.*Midwifery oral assessment:* As part of the antenatal check-up, midwives (trained in oral assessment) assess the oral health status of pregnant women using the following oral assessment tool. The tool consists of two questions and a visual inspection of the oral cavity (see Figure 1).

**Figure 1 Fig1:**
[figure not shown]
**The midwifery oral assessment tool.**

A total score ≥ 1 for the two questions, indicates that the pregnant woman is at risk of dental problems and requires referral to a dentist. The second question is also a cue for where to refer the pregnant women (ie. private/public or health fund) and is relevant for participants in Intervention group 1 (IG1). As highlighted in our preliminary research [32] visual inspection of the oral cavity helps confirm any oral health concerns raised by the pregnant women and provides an opportunity to identify any other dental issues that may be present. The two questions have been recommended in published perinatal oral health practice guidelines [33] and utilised in previous prenatal oral health programs [34, 35]. Similar questions have also been used as a screening tool in other at-risk populations to detect poor oral health and have demonstrated adequate validity [36]. Our pilot study has shown that the tool has sufficient sensitivity to identify dental problems and facilitate referrals [25].

#### Referrals

In this group, all pregnant women assessed to be at risk of poor oral health are referred to current dental services (either private, public or health fund) for treatment. The referral letter provided to pregnant women includes a covering letter and a survey/checklist—date of first visit, total number of visits required, treatment completed (item numbers), and dentists contact details—to be completed by the dentists and returned to the study investigators via fax. Information on the survey/checklist is also sought from private dentists whose contact details are provided by pregnant women in the post questionnaire. The checklist helps to assess the uptake of dental services, the common treatment requirements and associated dental costs, all of which are vital information to inform future economic evaluations and subsequent state and national policy in this area.

##### Intervention group 2 (IG2)

This group receives oral health promotional material at the time of recruitment. This group also receives a **midwifery and dental intervention** (MIOH-DS). The **midwifery intervention** will be similar to Intervention group 1. However, in this group all pregnant women, regardless of whether they are assessed to be at risk of having dental problems or not by the midwife, are referred (referral letter with checklist) to the dentists employed for this study for an initial dental oral assessment (part of the dental intervention). This allows for further testing of the midwifery oral assessment tool and to gather baseline oral health data. Pregnant women who consent are provided vouchers that entitle them to priority access to free oral assessment and treatment by the study dentists at dental clinics in the recruitment hospitals. This service is an extra service created specifically for this study and is co-ordinated by the study team. The voucher is valid for 4 weeks from booking visit date to encourage pregnant women to see the dentist promptly. Pregnant women can make the dental appointment by calling the telephone number provided with the referral letter or contacting the dental assistant in the antenatal waiting room.

##### Dental intervention

At the first appointment all the women undergo an initial dental oral assessment that includes medical history, followed by oral mucosal tissue examination, periodontal examination, dental caries examination and denture evaluation. A provisional diagnosis and treatment plan is made for those women having oral health problems. Once the consent for treatment is obtained, subsequent appointments are made in the second trimester to complete all the urgent treatment for women having dental problems. The second trimester (13–27 weeks) is considered a safe period to carry out necessary dental treatment^10^. The completion of treatment will take 1 to 3 additional visits depending on the treatment plan. Women having complex treatment needs such as root canal treatment are referred to the specialist for follow up care and are excluded from the study. After each examination participants are provided oral health education including oral hygiene instructions, brushing and flossing instructions and dietary counselling.

All women in the control group, intervention group 1 and group 2 (whether or not at risk of dental problems) undergo a final dental oral assessment by the study dentists at 28–38 week gestation period, the end point of this study. This examination is similar to the initial dental oral assessment and includes a detailed clinical examination. All women receive reminder cards from midwives followed up by telephone calls from the study administrative assistant to attend their final dental oral assessment. Pregnant women in the control group identified with a dental problem are referred to dental services after pregnancy. A post questionnaire having similar items to the pre questionnaire (demographic data, dental/medical aspects of the women’s health such as uptake of dental services, quality of oral health and post-test oral health knowledge), is administered to all women between 28–32 weeks. Contact details of private dentists who were consulted during pregnancy are also sought in the post questionnaire. The following methods are used to administer the post questionnaires: via the dental assistant/receptionist in the antenatal waiting room, via the midwife during the antenatal visit, over the phone when the final dental appointments are being made and via the study dentists at the final dental appointment.

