*Birth outcomes*: Gestational age at birth and birth weight is obtained from the ObstetriX data system (ODS) [41] which is a reliable data source (Kappa =0.75) using data items/definitions from the NSW Perinatal Data Collection (population based surveillance system covering all births in NSW public/private hospitals). Data from ODS is accessed using the women’s medical record numbers and date of birth (collected at recruitment) through local data custodians.*Specificity and sensitivity of midwifery assessment:* To further confirm the practicality of this tool, the midwifery oral assessment tool (2 items) will be compared with two gold standard measures- the OHIP-14 questionnaire (completed at the time of recruitment: pre-questionnaire) in IG1 and IG2 and the initial dental oral assessment conducted by the two study dentists in IG2. This will allow for women with and without oral health problems (the proportion of true and false positives and the proportion of true and positive negatives) to be identified. The OHIP-14 questionnaire has been used as the gold standard in previous studies to validate oral assessment tools [36, 42]. The two study dentists are trained to follow a standardised dental protocol during pregnancy. Adherence to the protocol is being evaluated by assessing the returned checklist.

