### Data analysis

Per-protocol and intention-to-treat analysis will be conducted by staff blinded to the group allocation. Missing data will be coded in the database structure and handled using an appropriate method. Demographic data will be analysed using descriptive statistics. All variables will be examined for normality and appropriate data transformations will be applied. Potential confounders (income, pre-existing oral health conditions, and others) and the impact of the MIOH/MIOH-DS intervention will be examined using univariate and multivariate methods. Regression analysis that take into account the variables of interests to the outcome will be performed. Some of the variables will be considered as exerting fixed effects (e.g. the number of patient groups) while others as random effects e.g. oral health knowledge. The regression models will also include a hospital variable (1–3). Analysis will be conducted for each hospital clinic and if no differences are found, data will be pooled. Pearson’s Chi-square test will be used to analyse the proportion of pregnant women accessing dental services. Oral health status and knowledge outcomes will be analysed using Analysis of Variance and post-hoc procedures. The effectiveness of the oral health education program will be assessed using dependent t-tests.

The sensitivity and specificity of the oral assessment tool using the OHIP-14 as the gold standard will be calculated using odds ratios. For this analysis the total scores using the midwifery oral assessment tool for participants in IG1 and IG2 will be dichotomised as 0=0 (no risk) and 1 to 2=1 (at risk). The total scores for participants using the OHIP-14 in IG1 & 2 will also be dichotomised using the median split as described by Locker et al. [42]. Subjects with an OHIP-14 score of 0–7 will be scored 0 (no risk) and 8–56 a score of 1 (at risk). Sensitivity and specificity will also be calculated using the initial dental oral assessment in IG2 as the gold standard. Analysis of proportions using chi square procedures (two tailed) and confidence intervals will be undertaken to determine sensitivity (true positives), specificity (true negatives), false positives, false negatives, negative and positive predictive values [46].

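### Women with complex dental needs are dropped from the study after randomisation, under a rule that can operate only in IG2

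*Protocol article*

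**What the plan says.** - **Exclusion rule.** Protocol article, Dental intervention: women with "complex treatment needs such as root canal treatment are referred to the specialist for follow up care and are excluded from the study".
- **Timing.** Under Randomisation, allocation follows consent and the baseline questionnaires. No dental examination has taken place by then. Complex dental need is not among the eligibility criteria under Participants and recruitment.
- **IG2.** All women in this arm, whatever the midwife's finding, "are referred (referral letter with checklist) to the dentists employed for this study for an initial dental oral assessment (part of the dental intervention"). The Outcome measures section again places this examination in one arm: "the initial dental oral assessment conducted by the two study dentists in IG2".
- **IG1.** Under Referrals, "all pregnant women assessed to be at risk of poor oral health are referred to current dental services (either private, public or health fund"). Outside dentists return a checklist. No exclusion is attached to it.
- **Control.** There is no dental examination before the final assessment. Women found then to have a problem are referred after pregnancy, not excluded.
- **Analysis.** Data analysis: "Per-protocol and intention-to-treat analysis will be conducted by staff blinded to the group allocation". The section does not say how the excluded women are handled.
- **Follow-up.** The Dental intervention section also states that all women in the three groups have the final dental assessment, and that the post questionnaire goes to all women.

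**The concern.** Randomisation makes the three arms comparable in oral-health severity, and stratifying by presence of a dental problem reinforces this. The exclusion undoes it in one arm. A woman with complex needs who is allocated to IG2 and attends is removed. Her counterpart in IG1 or the control group stays and is counted.

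Uptake of dental services and oral health are two of the three parts of the primary hypothesis, and the rule affects them in opposite directions:

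- **Uptake.** A woman can be excluded only after attending the study dentist. Each removal deletes a certain success from IG2.
- **Oral health status.** The women removed are likely to have worse mouths than average. The rest of IG2 then look healthier at the final assessment even if treatment did nothing.

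The IG2 comparisons with the control group and with IG1 are both affected. The IG1 comparison with control is not.

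**Working it through.** **1. The plan's own figures.** Inputs from Sample size: 30% against 50% uptake, two-sided alpha 0.017, 80% power. With z = 2.387 and 0.842, pooled variance and no continuity correction:

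n = [2.387·√(2·0.40·0.60) + 0.842·√(0.30·0.70 + 0.50·0.50)]² / 0.20² = 123.7, so 124 per group (power 80.1%).

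Recruitment: 124/(1 − 0.40) = 207 per group, 621 in all. The stated figures reproduce. The 40% allowance covers refusal (10%) and loss at the endpoint (30%), is the same in every arm, and does not mention exclusion for complex needs.

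**2. Effect on uptake.** Let f be the share of all IG2 women excluded. The protocol gives no value, so 2%, 5% and 10% are assumed. All of them attended, so with a true uptake of 50%:

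observed uptake = (0.50 − f)/(1 − f)

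Power is for a pooled z-test at alpha 0.017, with 124 control women at 30% and 124(1 − f) women in IG2. The last column removes the same number of women but leaves uptake at 50%.

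| f (assumed) | f as share of attenders (f/0.50) | Observed IG2 uptake | Power | Power from lost numbers alone |
|---|---|---|---|---|
| 0 | 0 | 50.0% | 80% | 80% |
| 2% | 4% | 49.0% | 75% | 80% |
| 5% | 10% | 47.4% | 65% | 79% |
| 10% | 20% | 44.4% | 46% | 78% |

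Almost all of the power loss comes from bias, not from smaller numbers, so recruiting more women would not remove the cause.

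**3. Effect on gingival bleeding.** Assume no treatment effect, 50% bleeding overall (the protocol's control rate) and 80% bleeding among the excluded women (assumed).

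observed IG2 bleeding = (0.50 − 0.80f)/(1 − f)

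| f (assumed) | Observed IG2 bleeding | Spurious benefit (points) | Rejection rate at nominal 1.7% |
|---|---|---|---|
| 2% | 49.4% | 0.6 | 1.75% |
| 5% | 48.4% | 1.6 | 2.0% |
| 10% | 46.7% | 3.3 | 3.2% |

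Rejection rates use 124 control women and 124(1 − f) in IG2.

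**4. Sensitivity to true uptake.** The protocol treats 50% as the least that counts as success. If true IG2 uptake were 60% (assumed), observed uptake = (0.60 − f)/(1 − f) = 59.2%, 57.9% and 55.6%. Power is then 99%, 98% and 95%, against 99% with no exclusion.

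**The case against.** The strongest reply is that the exclusion may mean only that these women leave the study's dental treatment when they pass to a specialist. The next paragraph of the same section gives the final assessment to all women in the three groups, and intention-to-treat analysis is named. That reading is possible, but it is not what the sentence says. The passages conflict, and a site following the sentence literally would stop collecting the woman's outcomes, which no later analysis plan can recover.

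Second, attendance at the study clinics is recorded in their own database, which is a listed source for uptake. An intention-to-treat analysis could count these women without further contact. This stands: the uptake bias arises only if data already held are set aside. Being excluded from the study invites that, and final oral health has no such fallback.

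Third, complex needs could also be noticed elsewhere, through IG1 checklists or at the final examination in any arm. That is correct, but no exclusion follows in those cases. The asymmetry lies in the rule.

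Fourth, the size. The fall to 46% power needs one IG2 attender in five to be excluded with true uptake at exactly 50%; at 60% uptake, power stays at 95% or more. The uptake bias works against IG2, so it is conservative. The bleeding bias is small beside the planned 30-point difference, and the 80% bleeding rate has no support in the protocol. All of this limits the size, but neither the existence of the one-arm exclusion nor the direction of the uptake bias. The 50% against 30% case is also the one on which the trial is sized.

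**Conclusion.** The concern holds. As written, the protocol removes randomised women on grounds of oral-health severity, after an examination that only IG2 receives, and this cannot be squared with intention-to-treat analysis or with a final assessment for all women.

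If the excluded women are left out of the analysis, the direction for uptake is certain: IG2 is understated. For oral health, IG2 is flattered provided the excluded women have worse mouths than the rest, which is likely but not documented.

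The size is unknown, because no rate of complex needs is given. In the plan's own design case, an assumed 5% exclusion lowers observed uptake by 2.6 points (50.0 − 47.4) and power by about 15 points (80 − 65). The spurious bleeding benefit at that share is 1.6 points. No stated sample-size figure is wrong.

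**What to change.** Replace the exclusion wording in the Dental intervention section. State that women referred to a specialist for complex needs remain in the study, are invited to the final dental assessment and post questionnaire like everyone else, have their attendance at the study dentist counted as uptake, and are analysed in IG2. If an analysis without them is wanted, confine it to a labelled sensitivity or per-protocol analysis. Which population is primary can be left to the statistical analysis plan, provided the protocol does not end these women's follow-up.

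The cost is small: a change of wording, plus follow-up contacts that the protocol already plans for every participant. The 124 evaluable and 207 recruited per group, and the total of 621, are unchanged. The referral to a specialist is untouched.

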### Randomisation

Following consent and baseline data collection participants are allocated to the groups using block randomisation. This form of randomisation is recommended for large trials [29] and has been used in a number of recent trials in this research area [21]. A permuted block randomisation scheme with a random mixture of block sizes is used to set the allocation order, stratifying participants by hospital and presence of a dental problem. Block randomisation ensures that the number of participants in each arm of the trial will be evenly balanced [29]. Randomisation of participants is accomplished centrally using an independent computerised service which is accessed via the telephone at the time of recruitment.

Group allocation (IG1, IG2, CG) is represented by coloured stickers concealed in serially numbered opaque randomisation envelopes. After recruitment, baseline data collection and randomisation via telephone, the dental assistant hands over the randomisation envelope to the pregnant women, who then gives it to the midwife. All midwives at each of the hospitals are aware of which group each coloured sticker represents. To maintain allocation concealment and minimise selection bias the dental assistants are unaware of the colour codes and block sizes used for randomisation. In addition, the study investigators are blinded to group allocation. Due to the randomisation method, pregnant women attending on the same day receive different interventions.

To minimise any distress among pregnant women and maintain equipoise [30], oral health promotion material are provided via the dental assistant at recruitment to all trial participants. Women who refuse to participate are also provided with oral health promotional material. It is also possible that women attending the antenatal clinic on the same day might interact with each other which can lead to potential contamination (estimated at <5%) in the study. We are adjusting for this contamination during analysis [31] and have also included an item in the post questionaire asking if they have discussed their particpation in the study with other women attending the antenatal clinic at the same time. Analysis is being undertaken excluding such women.

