##### Education for midwives and dentists

Prior to the commencement of the trial all midwives from participating hospitals undertake the specific oral health education program endorsed by the Australian College of Midwives [18]. Midwives have to complete the program and competency assessment to ensure that they have adequate knowledge of oral health and are competent to undertake an oral visual inspection. Prior to the trial the two study dentists employed for the study participate in a two hour education workshop where they are trained by an experienced dental clinician to follow a standardised dental protocol during pregnancy. Training is also provided on the use of the oral health status measures. Inter-rater reliability testing of the dentists’ oral health assessments will be examined using 10 mock oral assessments.

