This multicentre randomised controlled trial, with participant and researcher concealment, will provide initial evidence of the efficacy of this intervention for large health services throughout Australia or elsewhere. The intervention, if found effective, will readily translate into clinical guidelines and policy for further national consensus. Data are also being captured to undertake a cost-benefit analysis to support subsequent lobbying of state or federal Australian governments for this initiative. This initiative—midwife assessessment and referral to dental services [vouchers and/or localised dental services]-may represent a cost-effective oral health policy that appropriately targets and long-term improves the oral health of Australian children.

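### The two study dentists who assess and treat IG2 also score the final oral examination in all three arms, with no rule separating the roles, so IG2 contrasts on examined oral health are open to detection bias

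*Protocol article*

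**What the plan says.** - **Who treats IG2.** The section on Intervention group 2 offers these women "free oral assessment and treatment by the study dentists at dental clinics in the recruitment hospitals". All of them are referred there, whatever the midwife's assessment shows.
- **How many dentists.** The section on education for midwives and dentists states that "the two study dentists employed for the study participate in a two hour education workshop". Their inter-rater reliability is to be examined on 10 mock assessments.
- **Who scores the end point.** Under Dental intervention, women in all three arms "undergo a final dental oral assessment by the study dentists at" 28–38 weeks, which the article names as the trial's end point.
- **What is scored.** Outcome measures lists the Sulcus Bleeding Index, clinical attachment loss, the Approximal Plaque Index and DMFT.
- **Where the other arms go.** IG1 women judged at risk are referred to existing private, public or health fund services. Control women receive promotional material only and are referred, if needed, after the trial.
- **What is said about masking.** Under Randomisation, "the dental assistants are unaware of the colour codes and block sizes used for randomisation", and the investigators are described as blinded. Data analysis assigns the analyses to blinded staff. The Discussion describes the trial as one "with participant and researcher concealment".

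**The concern.** Oral health is the second of the three parts of the primary hypothesis and has its own sample-size calculation, based on gingival bleeding. It is measured by an examiner's judgement. An examiner who knows that a woman is in IG2, and who carried out her care, may score her more favourably without meaning to. IG1 and control women get no matching leniency, because the same dentist meets them for the first time at the end point. The error would favour IG2, the arm with the full service, and no later analysis could separate it from a real effect.

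**Working it through.** **1. The plan's own figures.** With the pooled-variance formula for two proportions, no continuity correction, two-sided alpha 0.017 (z = 2.387) and 80% power (z = 0.842):

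n = [z_α √(2p̄(1−p̄)) + z_β √(p1(1−p1) + p2(1−p2))]² / (p1 − p2)²

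- Uptake, 30% v 50%: 123.7, so 124 per group, as stated.
- Gingival bleeding, 50% v 20%: 51.3, so 52 per group, as stated.
- Losses of 10% + 30%: 124/0.60 = 206.7, so 207; 52/0.60 = 86.7, so 87; 3 × 207 = 621. All as stated.

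None of these figures is in dispute. They fix the scale for step 4.

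**2. Can the examiner infer the arm?** Before the end point, a woman's contact with the study dentists depends on her group:

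| Group | Referred to the study dentists before the end point | Examined by them at the end point |
|---|---|---|
| IG2 | yes, all women | yes |
| IG1 | no (existing services) | yes |
| Control | no | yes |

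A woman the dentist has already treated under the trial is therefore in IG2. An unfamiliar woman could be IG1, control, or an IG2 woman who did not attend or who saw the other dentist. The inference identifies IG2 only; nothing lets the dentist tell IG1 from control. Of the three pairwise comparisons behind the alpha of 0.05/3, the two that involve IG2 are exposed.

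**3. Which outcomes are exposed?** The examined measures are. Uptake draws on checklists, clinic databases, the questionnaire and contact with private dentists. Birth outcomes come from a perinatal data system. Neither depends on the dentist's clinical scoring.

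**4. Scale, as illustration only.** The documents give no rate of misscoring. Assume no true effect, true bleeding of 50% in both arms (the plan's control rate), and under-calling of a share u of true positives in IG2 only. Let f be the share of IG2 women examined by someone who has treated them.

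Spurious difference = 0.50 × u × f

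- f = 1: u = 10% gives 5 points (50% v 45%); u = 20% gives 10 points (50% v 40%). Against the 30-point design difference these are one sixth and one third.
- f = 0.5: the same values of u give 2.5 and 5 points. A value well below 1 is plausible, since there are two dentists and the plan's success criterion needs only 50% of the group to use dental services.

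For a spurious difference b, the chance of a significant result is Φ((b − z_α·se0)/se1) + Φ((−b − z_α·se0)/se1), where se0 and se1 are the pooled and unpooled standard errors. For b = 0.10 and n = 124, se0 = 0.0632 and se1 = 0.0629. The first term is Φ((0.10 − 0.1508)/0.0629) = Φ(−0.81) ≈ 0.21, and the second is negligible.

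| Spurious difference | 124 per group | 52 per group |
|---|---|---|
| 0 | 1.7% | 1.7% |
| 2.5 points | 2.6% | 2.1% |
| 5 points | 5.6% | 3.2% |
| 10 points | 21.0% | 8.6% |

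**The case against.** The best reply is that the document never promises blinded dental assessors. It claims concealment from the assistants, blinded investigators and blinded analysts. The Discussion phrase is loose, and its word for researchers may mean only the investigators. That stands: a reader might infer a broken promise of assessor blinding, and the text does not support that. The weakness lies in the design itself, and the Discussion phrase is merely too broad. Nor can a condensed article be blamed for omitting detail; but here the article itself gives both roles to the same dentists.

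Three further inferences go beyond the text:

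- **The recruiter can foresee allocations.** IG2 women may book by "contacting the dental assistant in the antenatal waiting room", and the assistants also recruit. But the assistant learns this only after allocation, and only for women who book that way. Randomisation is central, by telephone, in strata, with mixed block sizes hidden from the assistants. Knowing some past IG2 members says little about the next assignment.
- **The knowledge test follows teaching.** Education after each examination is described in the paragraph on IG2's initial assessment and treatment. The final visit is one of four routes for the questionnaire, and no order is given there. This justifies a precaution and is not an established error.
- **All outcomes are unblinded and biased.** Steps 2 and 3 of the working show the narrower scope.

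It is also fair to say that participants in a referral and treatment trial cannot be masked. That is no defect, but it should not be described as concealment.

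**Conclusion.** The point holds in a limited form. The same two dentists treat IG2 and score the final examination in every arm, with no rule that separates or masks the roles. The examined oral-health measures are therefore open to detection bias in IG2 versus control and IG2 versus IG1. IG1 versus control, uptake and birth outcomes are not shown to be affected.

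The direction would probably favour IG2; the size is unknown. The 5–10 points, and the 5.6% to 21.0% chance of a false positive at 124 per group, rest on assumed under-calling of 10–20%, no true effect, and every IG2 woman being seen again by her own dentist. If half are, 2.5–5 points and 2.6% to 5.6% apply. It is worth correcting because an examined part of the primary hypothesis is at stake and existing staff can reduce the risk.

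**What to change.** 1. **Separate treating from assessing, for all arms alike.** At each clinic, have the final assessments of IG1, IG2 and control women done by the dentist who did not treat that clinic's IG2 women; for example, the two dentists swap clinics for final assessments. Do not cross over IG2 women alone: that could confound examiner with arm, and agreement between the two is examined on only 10 mock assessments. The article does not say how the dentists are deployed, so the swap needs one treating dentist per clinic to be settled first.
2. **Mask the record.** Use an assessment form without arm or treatment records.
3. **Order the visit.** Where the post questionnaire is given at the final dental appointment, have it completed before the examination and any education.
4. **Correct the Discussion.** Replace "with participant and researcher concealment" with a statement that allocation was concealed before assignment, that investigators and analysts are blinded (as Randomisation and Data analysis say), and that participants, midwives and treating dentists are not. Wording that only the analysts are blinded would contradict the Randomisation section.

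Leave the IG2 booking routes as they are: the threat is small, and changing access could affect uptake, itself a primary outcome.

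**Cost.** Scheduling and travel for two existing dentists; no added staff, visits or procedures. Change within IG2 from initial to final examination would then be scored by different examiners, although the comparison between arms at the end point would not suffer. Masking remains partial, because women may mention their care and recent dental work may be visible.
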